## Abstract

A study protocol is presented for the investigation of meditative movement (MM) as a treatment for pulmonary dysfunction in flight attendants (FA) who were exposed to second-hand cigarette smoke while flying before the smoking ban. The study will have three parts, some of which will run concurrently. The first is a data gathering and screening phase, which will gather data on pulmonary and other aspects of the health of FA, and will also serve to screen participants for the other phases. Second is an exercise selection phase, in which a variety of MM exercises will be taught, over a 16-week period, to a cohort of 20 FA. A subset of these exercises will be selected on the basis of participant feedback on effectiveness and compliance. Third is a 52-week randomized controlled trial to evaluate the effectiveness of a digitally delivered form of the previously selected exercises on a group of 20 FA, as compared with an attention control group. Outcome measures to be used in all three parts of the study include the 6-min walk test as a primary measure, as well as a range of biomarkers, tests, and questionnaires documenting hormonal, cardio-respiratory, autonomic, and affective state. This study is registered at ClinicalTrials.gov. Identifier: NCT02612389.

## Background

### COPD and Its Co-Morbidities in FA

Chronic obstructive pulmonary disease (COPD) is a major cause of morbidity and mortality worldwide; the primary cause of COPD is exposure to cigarette smoke. Those exposed to second-hand cigarette smoke (SHCS) are at increased risk for respiratory, cardiovascular, and other organ system disease that are similar to those suffered by smokers (1). Many flight attendants (FA) who flew before the ban on smoking in commercial aircraft, and who were thus exposed to SHS, have abnormal pulmonary function consistent with mild COPD, despite not meeting the GOLD criteria of reduced FEV1/FVC ratio (2). They also show increased rates of many of the co-morbidities associated with COPD, such as chronic bronchitis, cardiovascular disease, skin cancer, and depression and anxiety (3). The co-morbidities of COPD exacerbate and are exacerbated by the COPD (4). Thus, consideration of the co-morbidities of COPD is an essential aspect of its treatment (4). Significant co-morbidities include cardiovascular disease (4); depression and anxiety (5); muscle weakness, osteoporosis, skin and lung cancer, and diabetes (4); as well as autonomic disturbance (6), systemic inflammation and cachexia (4); frequent hypoxia, dyspnea, and disturbed breathing patterns (7); and disturbed posture and movement (8); see Figure 1.

**Figure 1 F1:**
[figure not shown]
**Reciprocal influences of core COPD pathology and the co-morbidities of COPD**.

### The Autonomic Nervous System in COPD

Autonomic dysfunction (AD) is known to be associated with COPD and most of its co-morbidities (6, 9–15); see Figure 2. Most of the diseases known to be co-morbidities of COPD may be caused or exacerbated by AD; for instance, cardiovascular disease (15, 16); hypoxia (17, 18); disturbed respiratory patterns (7, 19, 20); disturbed posture and movement patterns (21, 22); diabetes (17); immune function (4); airways restriction (6, 23); and anxiety and depression (12).

**Figure 2 F2:**
[figure not shown]
**Relationships of autonomic dysfunction to the co-morbidities of COPD**.

### Meditative Movement

Qigong, a traditional Chinese health practice, has been used in China for hundreds of years in treating those with respiratory disease (24). Recently, a case has been made for a novel category of exercise “meditative movement,” (MM) of which Qigong, Tai Chi, and Hatha Yoga are examples (25). Significantly, MM is hypothesized to act via its effect on the autonomic nervous system (ANS) (26, 27), as well as on neuromuscular control (28, 29), musculoskeletal condition (30), and mental state (31).

Meditative movement has been shown to be an effective intervention for COPD (30, 32–36) and equivalent or superior to conventional pulmonary rehabilitation in benefiting several symptoms of COPD (37).

Meditative movement may also be of benefit in many co-morbidities of COPD, such as heart disease risk factors (38, 39), hypertension (39, 40), depression and anxiety (26, 41), diabetes (42), osteoporosis (43), and muscle weakness (44), as well as reduced immune function (45, 46), inflammation (47, 48), and autonomic imbalance (49). Many of these beneficial effects may happen via the influence of MM on the ANS (26, 50); see Figure 3.

**Figure 3 F3:**
[figure not shown]
**Hypothesized pathways of direct and indirect influence of MM on co-morbidities of COPD**.

### Study Aims

To evaluate COPD-related health factors in FA exposed to SHCS while flying, and to determine the effects of digitally delivered MM training on these factors.

There are three sub-aims, relating to the three main aspects of the study:
(1)To investigate the hypothesis that COPD-related pulmonary and other symptoms in SHCS-exposed FA are part of a syndrome of related disorders.(2)To determine that MM practices are most suited to and effective for ameliorating pulmonary dysfunction and related health problems in FA exposed to SHCS.(3)To conduct a randomized controlled trial (RCT) to determine whether this specifically adapted MM training can be effectively delivered digitally, providing the benefits of MM without face-to-face instruction being necessary.

## Methods

### Overall Structure of the Study

This study has three stages: Screening, Selection, and RCT. Screening will continue throughout the study and will gather data as well as serving to provide participants for the other Selection and RCT stages. The RCT will follow the Selection stage. All aspects of this study have been approved by the Dartmouth IRB. Additionally, this study is registered at ClinicalTrials.gov Identifier: NCT02612389. https://clinicaltrials.gov/ct2/show/NCT02612389/

#### Screening

To screen a cohort of FA exposed to SHCS for a range of biomarkers and symptoms to determine whether symptom clusters exist that suggest a syndromal entity.

##### Rationale

Flight attendants exposed to SHCS have been observed to display a wide range of respiratory, functional, inflammatory, autonomic, cardiovascular, affective, and other symptoms. The possible relationship between these symptoms has not previously been explored. We hypothesize that these symptoms may be correlated and form a syndromal entity.

#### Selection

To determine which of a variety of possible MM exercises are most effective in improving specific outcome measures, most enjoyable, and most likely to be practiced in a cohort of FA exposed to SHCS and having a degree of pulmonary dysfunction. This is done by conducting a 16-week in-person MM training program that is held in the Northeastern region of the US. Participants provide extensive feedback on the exercises.

##### Rationale

Meditative movement offers an inexpensive intervention that could benefit pulmonary symptoms and other related symptoms, through its effect on the ANS, cardiovascular, and immune systems. However, there is a large body of possible MM exercises, and there has been no investigation of the relative effectiveness, acceptability, and compliance among FA for the many MM exercises that are traditionally recommended for COPD-related symptoms. To our knowledge, no other study has attempted to evaluate a wide range of MM practices to determine which are most appropriate for the population being studied.

#### Randomized Controlled Trial

To develop a DVD or other digital form for delivering the selected exercises that have proven to most appropriate for this population, and to test by RCT the effectiveness of this digital format in improving specified outcome measures in a group of FA with pulmonary dysfunction and exposed to SHCS, as compared to a matched attention control group who will watch educational digital material of similar length.

##### Rationale

Selecting appropriate exercises and providing face-to-face instruction in MM offers significant difficulty due to the lack of trained teachers in most areas of the country and the practical demands of attending classes. A digitally delivered format would make this intervention much more accessible, and an RCT will evaluate the effectiveness of this intervention.

### Participants

#### Recruitment

Flight attendants were recruited from the Northeastern region and other areas of the US for the Selection stage; the Screening and RCT stages will involve recruitment throughout the continental US in locations convenient to data collection points. Primary outreach is through existing FA organizations and networks, social media, and FA publications, as well as in conjunction with the Harvard Flight Attendant Health Study. Social media support is also provided by Department of Health Behavior at the Roswell Park Cancer Institute in Buffalo, NY, USA.

#### Randomization and Blinding

The Screening and Selection stages of this study do not use a control group; blinding and randomization are, therefore, not necessary. In the RCT, participants will be stratified by gender, age, and severity of pulmonary dysfunction and randomized to an intervention groups and an attention control, using the covariate adaptive randomization method (51). This method accommodates recruitment and testing over an extended period of time. Full blinding of participants to intervention is not possible under these circumstances; however, all scoring of tests will be done by assistants blinded as to participant group.

#### Inclusion Criteria

The Screening stage of the study acts both to collect participant baseline data and to determine eligibility for the Selection and RCT stages.

All participants must be current or former non-smoker FAs employed by a US carrier for at least 5 years while smoking was permitted in the aircraft cabin. They must have a score of above 5 on the COPD assessment test (CATest); this will eliminate those with no detectable pulmonary issues. A score of 5 is a low score, indicating minimal level of pulmonary dysfunction.

Many FA exposed to SHCS have detectable pulmonary abnormalities despite not meeting Gold criteria for mild COPD (2); we wish to include this population, since they are likely at risk for the future development of COPD or its co-morbidities. We will eliminate any participants not meeting at least one of the following spirometric criteria: ratio of forced expiratory volume in 1 s to forced vital capacity (FEV1/FVC) < 0.70; OR forced expiratory flow (FEF) at 25–75%, volume <80% of predicted normal; OR FEF at 50%, volume <80% of predicted normal; OR FEF at 75%, volume <80% of predicted normal. We will follow procedures as described by Arjomandi et al. (2) for determining normal FEF values.

Participants must be lifetime non-smokers, defined as having smoked <100 cigarettes in their lifetime. They must have a device on which to listen to audio or watch video instruction and be willing to do so; for the RCT portion of the study, capacity to watch online or DVD videos is required. Those who are pregnant, or who plan to become pregnant during the study, are excluded. Patients with cognitive impairment, severe emotional problems, or who are unable physically to perform the exercises are excluded. Participants will be asked not to modify their lifestyle significantly during the study period apart from the practice required by the study. Participants must all sign informed consent forms.

#### Sample Size

The Screening stage of this study has no limit on number of participants. For the Selection and RCT stages of the study, we determined that, based on a predicted difference of 46 m in the 6-min walk test (6MWT) and an assessment of previous similar studies of MM for COPD, this study required a sample size of 20 participants in each group to achieve a statistical power of 80% at a significance level of 5%. To compensate for anticipated dropout, we recruited a total of 27 participants into the Selection group. On the basis of our experience of a high dropout and non-compliance rate in the Selection stage (~40%), we intend to recruit 120 participants for the RCT, 60 for each group.

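### One figure of 20 per group for 80% power is given for both the one-arm Selection stage and the two-arm RCT; with a common SD of change it can be exact for only one, and 27 recruits leave about 16

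*Protocol article*

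**What the plan says.** The Sample Size section opens its calculation with "For the Selection and RCT stages of the study, we determined that", so one calculation covers both stages. It cites a predicted 46 m difference in the 6MWT and an assessment of earlier studies. It concludes that "this study required a sample size of 20 participants in each group to achieve a statistical power of 80" per cent, at 5% significance. It gives no SD, test or sidedness.

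The two stages have different designs. Under Randomization and Blinding: "The Screening and Selection stages of this study do not use a control group". The Pitfalls section describes the Selection results as pre- and post-intervention tests. The RCT compares intervention with attention control, using linear regression for the primary outcomes (Statistical Methods). Under Functional Ability, the 6MWT is scored as each participant's difference from baseline to end of study.

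On numbers, the Sample Size section says that, to allow for dropout, "we recruited a total of 27 participants into the Selection group". It then reports about 40% dropout and non-compliance in that stage, and on that basis plans 60 per group for the RCT. The Pitfalls section allows for up to 60% dropout. The Abstract describes the RCT as being "on a group of 20 FA, as compared with an attention control group".

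**The concern.** A one-arm test of mean change carries the sampling error of one mean. A two-arm comparison carries the error of two. For the same difference and the same SD of change, the two-arm design needs about twice as many participants per group. One figure of 20 at 80% power for both designs therefore fits at most one of them exactly, and the text does not say which.

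What is at stake is how the RCT's evaluable numbers should be read. If 20 is the two-arm requirement, the plan has room to spare. If 20 came from pre-post changes, 20 evaluable per arm would be well short of 80%, and the dropout allowance was built around the wrong target. Selection also falls below its own stated 20 at the loss rate that the section itself reports.

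**Working it through.** **Inputs.** Difference 46 m, power 80%, significance 5%, n = 20 per group, 27 recruited to Selection, loss about 40%, and 60 per RCT group (all from Sample Size); dropout allowance up to 60% (Pitfalls). Assumed: a two-sided test and one SD of 6MWT change, s, common to both stages.

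**The plan's own figure.** Without an SD, n = 20 cannot be reproduced forwards. It can only be solved backwards for the SD it implies.

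**Step 1: implied SD, normal approximation.** K = 1.960 + 0.842 = 2.802.

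- Two-arm: n = 2(sK/46)², so s = 46 / (2.802 × √(2/20)) = 51.9 m.
- One-arm: n = (sK/46)², so s = 46 × √20 / 2.802 = 73.4 m.

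The ratio is √2 whatever the inputs.

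**Step 2: implied SD, noncentral t.**

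- Two-arm: 46/s = 0.909, so s = 50.6 m.
- One-arm: 46/s = 0.660, so s = 69.7 m.

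**Step 3: power on each basis.** The noncentrality is 46√n/s for one arm (n − 1 df) and 46/(s√(2/n)) for two arms (2n − 2 df).

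| | 20 is the two-arm figure (s = 50.6 m) | 20 is the one-arm figure (s = 69.7 m) |
|---|---|---|
| Selection, n needed for 80% | 12 | 20 |
| Selection, power at 20 | 97% | 80% |
| Selection, power at 16 | 92% | about 69% |
| RCT, n per arm needed for 80% | 20 | 37 |
| RCT, power at 20 per arm | 80% | 53% |
| RCT, power at 24 per arm | 87% | 61% |
| RCT, power at 36 per arm | 97% | 79% |
| RCT, power at 60 per arm | above 99% | 95% |

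**Step 4: could both statements be exact?** Suppose the RCT compared final values instead of changes. With s = SD × √(2(1 − ρ)), where SD is the cross-sectional SD and ρ the pre-post correlation, one-arm n is proportional to 2(1 − ρ) and two-arm n to 2. These are equal only at ρ = 0. With baseline adjustment, two-arm n is proportional to 2(1 − ρ²), so the ratio to one-arm n is 1 + ρ, which again reaches 1 only at ρ = 0. A zero correlation between repeated 6MWT distances in the same people is implausible.

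**Step 5: headcounts.**

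- Selection: 27 × (1 − 0.40) = 16.2, about 16.
- Loss at which 27 still leaves 20: 1 − 20/27 = 26%.
- RCT: 60 × 0.60 = 36 per arm at 40% loss; 60 × 0.40 = 24 per arm at 60% loss.

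**The case against.** The strongest reply is that the wording about each group suggests a two-sample calculation. If so, the RCT has the power claimed, Selection has more than it needs even at 16, and no power claim fails. That stands as one of two readings the text allows. A reader might infer that the two statements simply contradict each other. The document does not support that without the assumption of a common SD, because it states no SD and does not fix the scale of the regression analysis.

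A reader might also infer that Selection misses its stated power. The documents show only a missed headcount. The 40% combines dropout with non-compliance, so non-compliant participants may still supply post-test data. Trial Status describes Selection recruitment as running through October 2015 and itself voices concern about completion. The main purpose of Selection is to choose exercises, and the Pitfalls section leaves controlled validation to the RCT.

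Third, a reader might infer that the RCT is underpowered. It plans 60 per arm, not 20. Even on the less favourable basis, power is 95% before loss and 79% at 40% loss; only losses near the 60% allowance bring it to 61%. Intent-to-treat analysis with multiple imputation means that the analysed number is not simply the completers, although imputation recovers information only as far as the observed data predict the missing walks.

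Lastly, an article may leave the SD to the full protocol. That is fair for the SD alone. It does not explain assigning one size and one power to two designs.

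**Conclusion.** The point holds conditionally. Given a common SD of 6MWT change and a two-sided 5% test, 20 per group delivers 80% power in at most one of the two stages as an exact requirement. In the other it is either generous (Selection at 97%) or short (RCT at 53% if only 20 per arm were evaluable). The text does not let a reader tell which.

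The Selection shortfall of about 16 against 20 follows from the section's own figures, with the caveat on non-compliance. It becomes a power shortfall (about 69%) only if 20 was the one-arm figure. The two harms do not arise on the two-arm basis at all.

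The Abstract's 20 matches the required number and the Sample Size section's 60 is the recruitment target. The mismatch is therefore one of presentation, but the Abstract does not say which number it means.

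This should be corrected, but the planned 60 per arm keeps it from being a critical fault.

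**What to change.** 1. Say which design the figure of 20 belongs to, and give the SD of 6MWT change, its source, the test and the sidedness.
2. Give separate calculations: a paired one for Selection and a two-sample one for the RCT, the latter matching the intended regression.
3. Restate Selection power at about 16 completers, or label its pre-post result descriptive.
4. State RCT power at the evaluable numbers that 60 per arm implies: 36 at 40% loss and 24 at 60% loss.
5. Reconcile the Abstract's RCT group of 20 with the 60 per group, saying which is the evaluable target and which is enrolment.

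The cost is a recalculation and some wording. A stated power may come out less favourable; no extra participants are asked for.

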### Interventions

The Screening stage of the study involves no intervention. In the Selection stage, the MM intervention is given in person in small groups (between 3 and 7), in 3-h classes, spaced 2–4 weeks apart, in locations convenient to the participants, for a total of 18 h of contact time over 4 months. Participant feedback will be solicited as to the subjective effectiveness, enjoyability, and likelihood of regular practice of each specific exercise.

The MM classes will be taught by one of the authors, [name], a Qigong teacher with over 40 years experience. In the classes, rather than teaching rote movements, the purpose and philosophy behind each exercise is explained. Suggestions are made as to how to set up a regular practice and how to integrate the exercises into everyday life. The participants are encouraged to ask questions and make comments on the exercises; all questions and comments are recorded in writing at the time. Individual attention is given to the needs of each participant, and written and audio explanations are also available to participants online. (Please see the Supplementary Material for the description of exercises from which we draw.)

The RCT stage of the study will involve the design of a digitally delivered intervention based on the exercises determined in the Selection stage to be most helpful. The intervention may be delivered on a DVD or through a web site. The goal will be to simulate as closely as possible the experience of attending a class through the development of innovative methods, such as computer animation, branching path selection, and user-controlled sequencing. Participants in the RCT will also have access to audio and written materials. Attention control subjects in the RCT will receive equivalent digitally delivered health education materials.

### Safety Considerations

Very few studies of MM have reported significant risks (52) and we do not anticipate any ill effects. Nevertheless, participants are instructed to discontinue the exercise immediately if they experience any of the following: dizziness, rapid or irregular heart-beat, sudden or excessive dyspnea, chest pain, significant pain anywhere in the body, and headache. In addition, during the classes we carefully monitor the participants for signs of distress, including facial paleness or redness, rapid breathing, sweating, or jerky movement. Any data gathered that suggest possible need for medical attention are drawn to the attention of the participants.

### Outcomes

These are the outcome measures to be used in the Screening stage of the study as well as to evaluate the effects of the MM practices in the Selection and RCT stages. The broad range of outcome measures will allow us to examine correlations between a wide range of variables representing a number of different physiological and psychological systems that may be involved in COPD and its co-morbid conditions.

#### Primary Outcome Measures

Six-minute walk testChange in high sensitivity C-reactive protein (hs-CRP)

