#### Functional Ability

Exercise endurance and tolerance is evaluated by the 6MWT followed by the Borg Dyspnea inventory. This is used as our principal outcome measure since it is a well-recognized measure of overall functional ability. The walk is conducted on an indoor level surface free of obstructions. Research assistants are on hand to assist participants with any difficulties. Maximum distance walked in 6 min is recorded (53–55). The difference in scoring from baseline to the end of study is calculated for each participant. *The Borg Dyspnea Inventory*, a well-established instrument for measuring respiratory distress, is administered following the 6MWT. The 6MWT is subject to variation due to motivation; the addition of the Borg instrument increases the reliability of the test.

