### Statistical Methods

Descriptive statistics, including mean, SD, and frequency, will be used to describe and summarize baseline data. We will also compare distributions between intervention and control groups in the RCT stage using Wilcoxon rank-sum tests and chi-square tests at baseline. An intent-to-treat analysis will be carried out where missing data will be handled by multiple imputation approach, and linear regression models will be used to compare the intervention group with the control group in terms of the primary outcomes.

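### Two primary outcomes are listed but only the 6MWT is sized, at an undivided 5%; if each is tested at 5% and either counts, false-positive risk reaches 9.75%

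*Protocol article*

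**What the plan says.** The Primary Outcome Measures section lists two items, which run together in the text as "Six-minute walk testChange in high sensitivity C-reactive protein (hs-CRP"). Statistical Methods uses the plural: linear regression will "compare the intervention group with the control group in terms of the primary outcomes". Anticipated Results foresees a significant improvement in each of the two.

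Other sections put the 6MWT first:

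- **Abstract:** "Outcome measures to be used in all three parts of the study include the 6-min walk test as a primary measure". Biomarkers follow among the remaining measures.
- **Functional Ability**, on the 6MWT: "This is used as our principal outcome measure since it is a well-recognized measure of overall functional ability".
- **Sample Size:** the only effect given is a 46 m difference in the 6MWT. Twenty per group are said "to achieve a statistical power of 80% at a significance level of 5" per cent. No effect or variability is given for hs-CRP.
- **Secondary Outcome Measures and Blood Analysis:** fingerprick blood analysis is listed as secondary with no exception, and CRP is one of the assays run on those blood spots.

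**The concern.** The outcome list and the analysis section give hs-CRP the same rank as the 6MWT. The sample size uses the whole 5% on the 6MWT, and the secondary list can be read as covering CRP too. These sections do not lead to one success criterion.

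The risk lies in a split result. If hs-CRP were significant and the 6MWT null, or the reverse, one reader could cite the outcome list and call the trial positive. Another could cite the sample size and the principal-measure statement and reach the opposite conclusion. If either outcome is allowed to count, the 5% in Sample Size is not the trial's false-positive rate.

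**Working it through.** **Inputs.** Two primary outcomes (Primary Outcome Measures). Significance level 5%, power 80%, difference 46 m, 20 per group (Sample Size). The sidedness and the SD are not stated; two-sided tests are assumed below. The article gives no correlation between the two test statistics, so a range is shown.

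**1. The plan's own figure.** The 20 per group cannot be reproduced without an SD, but the SD it implies can be found from n = 2(z₀.₉₇₅ + z₀.₈₀)² SD² / 46²:

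- (1.960 + 0.842)² ≈ 7.85
- SD = 46 / (2.802 × √(2/20)) ≈ 51.9 m (50.6 m with the t-test)

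Over assumed SDs of 40, 50, 60 and 80 m, the formula gives 12, 19, 27 and 48 per group. So 20 per group fits a full two-sided 5% spent on the 6MWT with an SD near 51 to 52 m. None of the 5% is set aside for hs-CRP.

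**2. Either outcome counts, each tested at 5%, neither has a true effect.**

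- Independent tests: 1 − (1 − 0.05)² = 1 − 0.9025 = 0.0975.
- Correlated tests: 1 − P(|Z₁| < 1.96 and |Z₂| < 1.96) under a bivariate normal.

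| Correlation | Chance of at least one false positive |
|---|---|
| 0 | 9.75% |
| 0.3 | 9.51% |
| 0.5 | 9.07% |
| 0.7 | 8.35% |
| 0.9 | 7.04% |

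**3. Other rules the text would also allow.**

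- Both must succeed: a false claim of success needs a false rejection on at least one outcome with no true effect, so the rate is at most 5%.
- The 6MWT alone decides: 5%.
- Level split equally, 2.5% each: 1 − 0.975² = 4.94% with independent tests.
- Fixed sequence, 6MWT first: if the 6MWT has no true effect, any false claim needs a false 6MWT rejection, at most 5%. If the 6MWT effect is real and hs-CRP has none, the only possible error is on hs-CRP, again at most 5%.

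**The case against.** The strongest reply is that this is a condensed article. A testing order or an alpha split commonly sits in the statistical analysis plan, which is not shown, so the absence of a multiplicity rule is not in itself a finding. That stands. What remains is that the article ranks the outcomes differently in different sections, and the choice of primary outcome and what the 5% covers belong in the protocol.

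The conflict is also softer than it first looks. The abstract calls the 6MWT a primary measure, which does not exclude a second one. A principal measure may simply be the first of two primaries. The secondary fingerprick entry may be meant for the other analytes (HbA1c, thyroid stimulating hormone, vitamin D). These readings are possible, but the text does not settle on them.

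Two stronger readings are tempting and are not supported:

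- *That the trial's false-positive rate is nearly 10%.* The 5% level appears once, in the 6MWT sample size. No section states a level for hs-CRP or says that one significant outcome is enough.
- *That sharing the 5% between two outcomes would leave the trial underpowered.* That needs an SD the article does not give, and it takes 20 per group as the final number. The plan is to recruit 60 per group; 40% loss would leave 36 and 60% loss would leave 24.

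**Conclusion.** The point holds in conditional form. The article names two primary outcomes and compares the arms on both, but it sizes the trial on one of them at the full 5%, calls that one principal, and lets CRP appear in the secondary tier as well.

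The inflation, to between about 7.0% and 9.75%, rests on three assumptions: both tests at an unadjusted 5%, success on either outcome, and a correlation between 0.9 and 0. Under the other readings in step 3 the rate is at or below 5%. The inconsistency itself is plain from the text; the size of the error depends on a rule the article does not state. It should be settled before the arms are compared.

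**What to change.** In Primary Outcome Measures, name the 6MWT change from baseline to end of study as the deciding primary outcome, tested at 5%. In Statistical Methods, state that hs-CRP is tested at 5% only if the 6MWT result is significant. Then align the abstract and both outcome lists, and say in the secondary list that the fingerprick entry means the analytes other than CRP, or place hs-CRP there explicitly.

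The cost is about two sentences plus the alignment. The 6MWT is tested first at the full 5%, so its power calculation is unchanged. The real loss is that a significant hs-CRP result with a null 6MWT could not be claimed as a positive trial. If the sponsor wants hs-CRP to keep equal rank, requiring both outcomes or splitting the 5% would also hold the error rate, but either choice would mean revisiting the sample size.
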